### Phase II

The second phase focused on the importance of medication adherence in achieving optimal BP control, a clinical update on hypertension management, motivational interviewing, review of BP monitoring by patients, downloading home BP recordings, charting BP against adherence, and identification and resolution of medication-related hypertension by MUR.

Pharmacists in the PCG were offered Phase II training before baseline data collection. The UCG pharmacists will receive Phase II training after the six-month follow-up, so that control patients can be offered the interventions tested in the PCG after the study. This will encourage recruitment of pharmacists to the UCG and improve retention of patients in the UCG.

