**Methods/Design:**

The HAPPY trial is a multi-centre prospective randomised controlled trial. Fifty-six pharmacies have been recruited from three Australian states. To identify potential patients, a software application (MedeMine CVD) extracted data from a community pharmacy dispensing software system (FRED Dispense^®^). The pharmacies have been randomised to either 'Pharmacist Care Group' (PCG) or 'Usual Care Group' (UCG). To check for 'Hawthorne effect' in the UCG, a third group of patients 'Hidden Control Group' (HCG) will be identified in the UCG pharmacies, which will be made known to the pharmacists at the end of six months. Each study group requires 182 patients. Data will be collected at baseline, three and six months in the PCG and at baseline and six months in the UCG. Changes in patient adherence and persistence at the end of six months will be measured using the self-reported Morisky score, the Tool for Adherence Behaviour Screening and medication refill data.

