### Cluster randomisation

In each state, pharmacies were randomised to either Pharmacist Care Group (PCG) or Usual Care Group (UCG) according to the PhARIA. Randomisation was carried out at the pharmacy level to avoid the contamination likely to result from the same pharmacy recruiting and following up both intervention and control group patients. Randomisation was carried out at a central location using the sealed opaque envelope technique. To check for any 'Hawthorne effect' [20,21] in the UCG due to the effect of data collection, a third group of patients (Hidden Control Group - HCG) who are taking or have taken antihypertensives in the previous six months (but not included as participants in the UCG) will also be identified.

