### Recruitment of patient participants

A software application, MedeMine CVD, has been installed on the dispensing computer of participating pharmacies. MedeMine CVD extracts data from the market leading pharmacy dispensing software system in Australia (FRED Dispense^®^) and identifies patients who are using or have used antihypertensive medicines in the previous six months. The purpose of MedeMine CVD is to:

1. preferentially identify patients who last had their antihypertensive medications dispensed more than 59 days previously and those with suboptimal refill adherence;

2. generate personalised "Expression of Interest" (EOI) forms to mail to potential patient participants. Once the completed EOI has been received by the pharmacist and eligibility is confirmed, the information is recorded in MedeMine CVD;

3. generate the participant explanatory statement and consent form, as well as a letter and fax-back form to be sent to the participant's GP to confirm diagnosis of primary hypertension and advise of the participant's target BP;

4. manage participant appointments by pharmacists;

5. create a unique identification number for each participant, which is printed on all study documents (e.g. data collection forms and letters); and

6. send SMS reminders or prompt the pharmacist to telephone or send mail reminders, to participants who have requested this part of the service, when their supplies are dwindling.

An invitation letter (EOI) with a short questionnaire (seeking information about the patient's BP, interest in participation, nominated GP, including contact details and consent to contact the GP, and patient telephone contact details) and a reply-paid envelope were sent to potential participants. Patients were asked to return the completed questionnaire to the pharmacy and indicate their interest in participating. Once the EOI is received, the pharmacist will contact the patient to further assess their eligibility and arrange a mutually convenient time to visit the pharmacy to enrol in the study. If eligibility is confirmed, the consent form would then be signed. The pharmacist will also contact the patient's GP. At no point are patients' identities made known to the researchers.

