### Exclusion criteria

• participation in other adherence promotion programs;

• having had a pharmacist-conducted HMR service in the last 12 months;

• unable to communicate in English; and

• does not self-administer antihypertensive medicines.

Each pharmacist was asked to recruit 7-10 patients from their pharmacy.

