### Data analysis

Participant characteristics in the UCG and PCG will be compared at baseline. Paired t-tests and/or Wilcoxon Signed Rank test will be used to compare changes in total scores on the Morisky scale, TABS and MedsIndex between the PCG and the UCG at baseline and six months. MedsIndex scores will be compared using paired t-tests and/or Wilcoxon Signed Rank test in the UCG and the HCG at six months.

Baseline data will be used to identify factors associated with suboptimal adherence in the whole study population. Significant factors in univariate analysis (chi-square, Mann-Whitney U test and Student's t-test) will be further tested in multivariate analysis (linear regression) to identify independent predictors of nonadherence/nonpersistence in the study population. To adjust for cluster randomisation, a pharmacy variable will also be included in the multivariate models.

An economic evaluation will also be carried out and will be reported elsewhere.

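### Patients are enrolled after pharmacies are allocated, so the arms can differ at entry, and the planned covariate-free comparison of score changes handles only part of that difference

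*Protocol article*

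**What the plan says.** **Allocation.** The abstract reports allocation as already done: "The pharmacies have been randomised to either" the pharmacist care group (PCG) or the usual care group (UCG). The Cluster randomisation section gives contamination as the reason: "Randomisation was carried out at the pharmacy level to avoid the contamination likely to result from the same pharmacy recruiting and following up" patients of both groups.

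**Training.** Phase I, which covers recruitment and use of the MedeMine software, went to all pharmacists. On Phase II, which covers the intervention, the article says "Pharmacists in the PCG were offered Phase II training before baseline data collection" and "The UCG pharmacists will receive Phase II training after the six-month follow-up".

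**Recruitment.** MedeMine gives preference to patients with a long dispensing gap or poor refill adherence and prints invitations, which are mailed. After a reply, "Once the EOI is received, the pharmacist will contact the patient to further assess their eligibility and arrange a mutually convenient time" for enrolment. The general practitioner is asked to confirm the diagnosis. The target is "Each pharmacist was asked to recruit 7-10 patients from their pharmacy", and an eligible pharmacy has at least 40 users of antihypertensives.

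**What patients are offered.** PCG patients receive a home blood pressure monitor and the package at baseline. UCG patients receive the package after their six-month measurements.

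**Analysis.** "Paired t-tests and/or Wilcoxon Signed Rank test will be used to compare changes in total scores" on the Morisky scale, TABS and MedsIndex between the two groups. Baseline characteristics are to be compared, with no consequence stated. The multivariate models that carry a pharmacy variable are for predictors of suboptimal adherence at baseline, not for the PCG–UCG effect.

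**The concern.** Randomising pharmacies balances pharmacies. It does not balance patients who are identified, approached and consented afterwards by staff who know the allocation. Differences at entry can arise without any deliberate selection: a pharmacist newly trained in motivational interviewing may present the study differently, and an immediate monitor and service may attract different people from a deferred one.

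If that happens, part of the six-month difference between arms reflects who was enrolled rather than what was done for them. The analysis named in the article uses no patient-level covariate, so its only protection is that it works on changes from baseline.

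**Working it through.** **1. Order of events.** Allocation is reported as complete, while eligibility assessment and enrolment are in the future tense. Phase II training reaches one arm before baseline and the other after six months. A pharmacist who has, or has not, had that training and who hands out the package at baseline must know the arm by the baseline visit. This is an inference from the schedule. The article does not say when invitations were mailed relative to allocation.

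**2. Room for differences.** 450 patients / 56 pharmacies = about 8 per pharmacy. Against the minimum pool of 40, the target of 7 to 10 is 7/40 = 17.5% to 10/40 = 25%. Most of the pool is not enrolled, even in the smallest eligible pharmacy.

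**3. The plan's own figure.** For 50% versus 65%, two-sided 0.05 and 80% power, with mean proportion 0.575:

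n = [1.96·√(2·0.575·0.425) + 0.8416·√(0.5·0.5 + 0.65·0.35)]² / 0.15² = 169.3

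Continuity correction: (169.3/4)·[1 + √(1 + 4/(169.3·0.15))]² = 182.4

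The stated 182 per group is reproduced and is used below.

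**4. What a change score leaves behind.** Suppose there is no treatment effect and the arms differ at baseline by δ = 0.2 SD (assumed). Let r be the correlation between baseline and six months (assumed 0.3 to 0.7).

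- If the difference is stable, it is still 0.2 SD at six months and the difference in change is 0.
- If it regresses, only r·δ remains at six months and the spurious difference in change is (1 − r)·δ in size.

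With SE = √(2(1 − r))·√(2/182), and the false-positive rate equal to P(|Z + bias/SE| > 1.96), ignoring clustering:

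| r | bias (SD) | SE | bias/SE | false-positive rate |
|---|---|---|---|---|
| 0.3 | 0.14 | 0.124 | 1.13 | 20% |
| 0.5 | 0.10 | 0.105 | 0.95 | 16% |
| 0.7 | 0.06 | 0.081 | 0.74 | 11% |

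The sign depends on which arm starts lower: the arm with the worse baseline appears to improve more.

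**5. Differential propensity to change.** This survives both change scores and baseline adjustment. To show the scale only, take a purely selective shift in six-month adherence around 50%. With SE = √(2·0.25·DE/182), cluster size 182/28 = 6.5 (28 pharmacies per arm assumed) and DE = 1 + 5.5·ICC:

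| assumed shift | ICC 0 | ICC 0.02 | ICC 0.05 |
|---|---|---|---|
| 5 points | 16% | 15% | 13% |
| 8 points | 33% | 31% | 27% |

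Five points is one third of the 15-point target. The columns with ICC above 0 assume a test that uses the correct, larger standard error. This table concerns six-month proportions, which is the scale of the sample size section and not the planned test of score changes.

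**The case against.** **Pharmacist discretion is narrower than it first looks.** A reader might infer that pharmacists hand-pick 7 to 10 patients. The article does not say so. Software targets candidates on dispensing data, invitations go by mail, patients select themselves by replying, and most criteria are factual (drug class, age, diagnosis, recent medicines review). Availability for follow-up leaves some judgement. Promising the same package later to UCG patients also reduces the difference in incentive. This stands. What remains is the pharmacist's contact, assessment and enrolment, and consent that may depend on the arm.

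**Knowledge of the arm at invitation is not documented.** A reader might take the training sentence as proof that invitations were sent with the allocation known. It refers to baseline data collection, and recruitment was taught in Phase I, which was the same for both arms. Only knowledge by the baseline visit can fairly be inferred.

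**Changes from baseline are already a form of protection.** This is true for a stable difference, and it is why calling the comparison simply unadjusted would overstate the point. Regression to the mean is still a live issue, because candidates are sought for poor recent refill adherence and the degree of that selection may differ by arm.

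**Covariates and invitation rules usually belong in the analysis plan or full protocol.** Silence on them would be no finding. Here, however, the article names the method for the PCG–UCG comparison and assigns its multivariate models to another question, so the stated method can be judged.

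**Pharmacy allocation and pharmacy-run recruitment were reasoned choices.** One avoids contamination and the other keeps patient identities from the researchers. Neither needs to be reversed.

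**Conclusion.** The concern holds as a risk that the stated analysis only partly handles. It rests on two inferences: that pharmacists know their arm by the baseline visit, and that an immediate offer in one arm and a deferred one in the other can change who enrols.

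Its size cannot be derived from the documents. The rates of 11% to 20% (regression to the mean after an assumed 0.2 SD imbalance) and 13% to 33% (assumed 5- or 8-point shifts in six-month adherence) are illustrations. A reader might quote them as this trial's false-positive rate, but no passage supplies a selection shift, an imbalance, a correlation or an ICC.

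The direction is also open. A reader might infer that any bias favours the PCG. If PCG pharmacies enrolled more motivated patients who were already adherent, those patients would have less room to improve and a change score could be biased against the intervention.

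**What to change.** **Analysis.** In the Data analysis section, replace the covariate-free comparison of changes with a between-group model for each six-month outcome. Adjust it for that outcome's own baseline value, baseline MedsIndex and days since last dispensing, and treat pharmacy as the cluster. Fix in advance how MedsIndex is summarised per patient, since it is scored per medicine. Baseline scores and MedsIndex are already collected, and the dispensing interval is of the kind MedeMine uses to find candidates, so the cost is wording and analysis time.

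**Sensitivity analysis.** Keep a between-group, cluster-adjusted comparison of changes. When an imbalance comes from selection rather than chance, the two methods rest on different assumptions. Baseline adjustment removes a difference that regresses, but it leaves (1 − r)·δ when the difference is stable (0.10 SD at δ = 0.2 and r = 0.5). The change score does the reverse. Agreement between them is reassuring, and disagreement should be reported.

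**Reporting.** Give the numbers invited, replied and enrolled by arm, where available. State that adjustment cannot remove selection on unmeasured motivation, and qualify the conclusion if enrolment patterns differ by arm.

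**Recruitment.** A fixed invitation order, the same in both arms, can help only for invitations not yet mailed; the article describes mailing in the past tense. It would not address consent that depends on the arm, and it may slow enrolment slightly.

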### Sample size

Australian, European and North American studies have estimated that around 50% of patients initiating an antihypertensive medication discontinue their medication (become nonpersistent) within twelve months [22]. To demonstrate a 15% difference in adherence between the control and intervention groups at six months (e.g. 50% in the UCG versus 65% in the PCG) with 80% power and a two-sided p-value of 0.05, 182 patients are required per study group. To allow for potential drop-outs (approximately 25% over six months) 225 patients need to be recruited per group; i.e. a total of 450 patients at baseline.

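### The 182 patients per group come from an individually randomised calculation, so the stated 80% power does not apply to a trial that randomises pharmacies

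*Protocol article*

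**What the plan says.** The Sample size section takes as its target a 15-point difference at six months ("e.g. 50% in the UCG versus 65% in the PCG") and concludes that "with 80% power and a two-sided p-value of 0.05, 182 patients are required per study group". It then makes one adjustment, for drop-out of about 25%, which brings recruitment to 225 per group and 450 in all. No ICC, cluster size or design effect is mentioned.

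The design is described elsewhere in the article:

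- Cluster randomisation section: "Randomisation was carried out at the pharmacy level to avoid the contamination" expected if one pharmacy handled patients of both groups.
- Abstract, Methods/Design: "Fifty-six pharmacies have been recruited from three Australian states".
- End of the Exclusion criteria section: "Each pharmacist was asked to recruit 7-10 patients from their pharmacy".

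**The concern.** Patients of one pharmacy share a pharmacist, a locality and, in the intervention arm, the same person delivering the package. That pharmacist also collects the outcome data. Their adherence outcomes are likely to be correlated, and correlated outcomes carry less information than the same number of independent ones. A calculation that treats 182 patients in about 28 pharmacies as 182 independent patients overstates power.

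What is at stake is how the result is read. A null finding would be presented as coming from a trial with an 80% chance of detecting a 15-point effect, when the real chance could be nearer 60% to 70%.

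**Working it through.** **Inputs from the article.** Control proportion p1 = 0.50, intervention proportion p2 = 0.65, difference d = 0.15, two-sided 0.05 (z = 1.960), power 80% (z = 0.8416), 182 analysed per group, 56 pharmacies, 7 to 10 recruits each.

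**Assumptions.** The pharmacies split equally, 28 per arm. Cluster sizes are equal at m = 182/28 = 6.5 evaluable patients. The ICC lies between 0.01 and 0.10. The article states none of these.

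**Step 1: reproduce 182.** With mean proportion 0.575, the two-proportion formula is

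n = [1.960·√(2·0.575·0.425) + 0.8416·√(0.50·0.50 + 0.65·0.35)]² / 0.15² = (1.3702 + 0.5816)² / 0.0225 = 169.3.

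The continuity correction gives

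n' = (n/4)·[1 + √(1 + 4/(n·d))]² = (169.3/4)·[1 + √(1 + 4/(169.3·0.15))]² = 182.4.

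Strict rounding up would give 183. At 182, power is 79.9% with the correction and 82.8% without. The stated figure is thus reproduced with independent patients and no design effect.

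**Step 2: apply clustering to 182.** The design effect is DE = 1 + (m − 1)·ICC and the effective size is 182/DE. Power is

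Φ{[d − 1/n − 1.960·√(2·0.575·0.425/n)] / √(0.4775/n)},

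with n the effective size; the term 1/n is dropped for the uncorrected version. At ICC 0.05, DE = 1 + 5.5·0.05 = 1.275 and n = 142.7. The argument is (0.1500 − 0.0070 − 0.1147)/0.0579 = 0.489, so power is 68.8%.

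| Assumed ICC | DE | Effective n per arm | Power, corrected | Power, uncorrected | 182 × DE |
|---|---|---|---|---|---|
| 0.01 | 1.055 | 172.5 | 77.6% | 80.7% | 193 |
| 0.02 | 1.110 | 164.0 | 75.3% | 78.7% | 203 |
| 0.05 | 1.275 | 142.7 | 68.8% | 72.9% | 233 |
| 0.10 | 1.550 | 117.4 | 59.3% | 64.4% | 283 |

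On the formula that yields 182, any positive ICC puts power below 80%. On the uncorrected test, power drops below 80% once the ICC exceeds about 0.014.

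**Step 3: detectable difference.** Solving the corrected power equation for p2 at 80% power, with p1 = 0.50, gives 17.0 points at ICC 0.05 and 18.7 points at ICC 0.10.

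**Step 4: what restoring 80% would take.** The last column of the table holds cluster size at 6.5 and so implies more pharmacies. With pharmacies fixed at 28 per arm, the number evaluable per arm is 182·(1 − ICC)/(1 − 182·ICC/28). At ICC 0.05 this is 172.9/0.675 = 256. At ICC 0.10 it is 163.8/0.35 = 468, or 16.7 per pharmacy, well beyond the 7 to 10 each was asked to recruit.

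**The case against.** The fairest counter-case has five parts.

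- **The origin of 182 is inferred.** The article names no formula, and the uncorrected 170 times a design effect of 1.07 (ICC 0.01, eight patients per pharmacy) also gives 182. This is arithmetically true, but the paragraph lists its inputs down to drop-out and none concerns clustering. Nothing in the text supports that alternative.
- **The loss may be small.** Without the continuity correction, power is 81% at ICC 0.01 and 79% at 0.02, close to the stated 80%. This stands. The omission is certain; its size is not.
- **More patients might be evaluable.** With 28 pharmacies per arm and 25% drop-out, 7 to 10 recruits each give 28·7·0.75 = 147 to 28·10·0.75 = 210 evaluable per arm. At 210 (7.5 per pharmacy), corrected and uncorrected power are 83% and 86% at ICC 0.01, 81% and 84% at 0.02, and 74% and 77% at 0.05. At 147, power is below 80% throughout. The upper end does not rescue the paragraph, which says that 182 is enough. The equal split and the 6.5 are rightly labelled as assumptions.
- **The percentages describe the stated binary scenario.** The Data analysis section compares total scores, and allocation by state and remoteness category may absorb some variation between pharmacies. Both are fair cautions against reading the table as the trial's exact power. They do not make the stated 80% correct.
- **A baseline ICC would be imprecise.** With 56 pharmacies of about eight patients, an ICC near 0.05 has a standard error of about 0.03. The baseline sample is also selected towards poor refill adherence. This stands too, so a baseline estimate should accompany a range and not replace it.

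**Conclusion.** The concern holds. The article attaches 80% power to 182 patients per group for a design that randomises pharmacies, and that number is the answer for individually randomised patients. With 28 pharmacies per arm and 6.5 evaluable patients in each, power runs from 78% at ICC 0.01 to 59% at ICC 0.10 on the formula that reproduces 182, or from 81% to 64% without continuity correction. The loss is modest at ICC 0.01 to 0.02 and serious at 0.05 to 0.10, and the article does not allow a choice between these. Unequal numbers per pharmacy would lower power further. The paragraph must be corrected, because the power claim is wrong as written and bears directly on how a null result is read.

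**What to change.** Rewrite the Sample size section as a cluster-trial calculation for the 56 pharmacies already recruited. State:

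1. the number of pharmacies per arm and the mean number of evaluable patients per pharmacy;
2. an assumed ICC for adherence, with its source and a range;
3. the design effect, and the resulting power for a 15-point difference or the smallest difference with 80% power;
4. the formula used, including whether a continuity correction applies.

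Estimate the ICC from the baseline adherence data, which involves no comparison of outcomes between arms, and report power at that value alongside the full range. The restated power assumes a between-group comparison that accounts for pharmacy. The Data analysis section names a pharmacy variable only for the multivariate models, so the two sections should be made to agree.

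The cost is a rewritten paragraph and a less favourable power or detectable difference. Enrolment and trial conduct need not change.

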### Six-month visit (Final project visit)

Measures performed at baseline will be repeated for both UCG and PCG patients at their six-month visit to the pharmacy.

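### Recruiting 225 per group does not protect the required 182 against 25% drop-out: about 169 remain, and 225 covers only about 19% loss

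*Protocol article*

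**What the plan says.** The Sample size section of the protocol article plans to detect a 15-point difference in adherence at six months, with the example "50% in the UCG versus 65% in the PCG", "with 80% power and a two-sided p-value of 0.05". From this it concludes that "182 patients are required per study group". The Methods/Design paragraph of the abstract repeats the requirement: "Each study group requires 182 patients".

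The Sample size section then makes its allowance for attrition: "To allow for potential drop-outs (approximately 25% over six months) 225 patients need to be recruited per group", giving 450 at baseline. It shows no inflation formula and gives no other reason for 225.

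On feasibility, the abstract reports 56 recruited pharmacies, and the end of the Exclusion criteria section says: "Each pharmacist was asked to recruit 7-10 patients from their pharmacy".

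**The concern.** A drop-out allowance should make the number recruited, less the expected losses, equal the number the power calculation requires. Here the requirement (182), the expected loss (25%) and the recruitment target (225) are all given, and at most two of them can be right together. A team that recruits exactly to plan and loses exactly the proportion it expected would finish below its own stated requirement.

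At stake are the accuracy of the recruitment target and the claim of 80% power under the plan's own attrition figure. The design itself is not in question on this point.

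**Working it through.** **Inputs, all from the Sample size section:** p1 = 0.50, p2 = 0.65, difference d = 0.15; two-sided alpha 0.05 (z = 1.960); power 80% (z = 0.842); required n = 182 per group; drop-out 25%; recruitment 225 per group, 450 in total. From the abstract: 56 pharmacies. From the end of Exclusion criteria: 7-10 patients requested per pharmacist, treated here as per pharmacy.

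**Step 1. Reproduce 182.** With mean proportion 0.575, the usual two-proportion formula is

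n = [1.960 × √(2 × 0.575 × 0.425) + 0.842 × √(0.50 × 0.50 + 0.65 × 0.35)]² / 0.15²
= (1.3702 + 0.5816)² / 0.0225 = 169.3, so 170.

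Applying the continuity correction:

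n' = (169.3/4) × [1 + √(1 + 4/(169.3 × 0.15))]² = 182.4.

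This is 182 to the nearest whole number, or 183 rounded up. Other two-sided versions without the correction give about 167 (unpooled variance) and 169 (arcsine), and one-sided versions give 134 or 147. So 182 comes from a two-sided continuity-corrected calculation, although the article does not name the formula.

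**Step 2. Check the drop-out step.**

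| Quantity | Arithmetic | Result |
|---|---|---|
| Evaluable per group from 225 at 25% loss | 225 × 0.75 | 168.75, about 169 |
| Shortfall against 182 | 182 − 169 | 13 per group |
| Recruitment needed at 25% loss | 182/0.75 = 242.7 | 243 per group, 486 in total |
| Gap to stated target | 243 − 225; 486 − 450 | 18 per group, 36 in total |
| Largest loss at which 225 keeps 182 | 1 − 182/225 | 19.1% |
| Mistaken shortcut n × (1 + loss) | 182 × 1.25 | 227.5, so 228 |

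The stated 225 matches neither the correct inflation (243) nor, exactly, the common shortcut (228). Even at 20% loss it leaves 225 × 0.80 = 180, still below 182.

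**Step 3. Power at 169 per group.** Power = Φ{(d − c − 1.960 × SE0)/SE1}, where SE0 = √(0.48875/n), SE1 = √(0.4775/n), and c = 1/n with the continuity correction or 0 without it.

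- With the correction, n = 169: (0.15 − 0.0059 − 0.1054)/0.0532 = 0.728, power 76.7%.
- Without it, n = 169: (0.15 − 0.1054)/0.0532 = 0.839, power 79.9%.
- For comparison, n = 182 gives 79.9% with the correction and 82.8% without it.

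The loss is therefore about 3 percentage points on either basis.

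**Step 4. Feasibility.** 486/56 = 8.7 patients per pharmacy, against 450/56 = 8.0 now. The existing request of 7-10 would yield 56 × 7 = 392 to 56 × 10 = 560. Both targets lie inside that range.

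**The case against.** The best defence is that little harm follows. The text says the loss is approximate, the article does not name its test, and an uncorrected comparison of 169 per group still has 79.9% power. It may even be that 225 was derived from an uncorrected n of about 169 (169/0.75 = 225.3) and then printed beside a corrected 182. That is a guess; the article does not say so.

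The point about size stands: the effect is modest, and a flat statement that 80% power is lost would depend on the choice of formula. The inconsistency remains, however. The word approximately does not stretch from 25% to 19%. If the uncorrected basis was intended, then 182 is the wrong figure, both in the Sample size section and in the abstract. Nor is this a matter that an article may leave to a fuller document, because all three numbers are printed.

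Two stronger readings should be resisted.

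- **The drop-out error leaves the trial badly underpowered.** A reader might infer this by adding a clustering penalty, since pharmacies are randomised and the Sample size section mentions no design effect. But any such penalty needs an intracluster correlation that the article does not give, and it would apply almost equally with the full 182 evaluable. It is a separate issue and should not be counted as a cost of this error.
- **Refill data are lost for patients who miss the last visit.** A reader might infer this from the Six-month visit section: "Measures performed at baseline will be repeated for both UCG and PCG patients at their six-month visit to the pharmacy". That sentence says when measures are repeated. It does not say that refill data are discarded for non-attenders, and a condensed article may leave that handling to the full protocol or analysis plan.

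**Conclusion.** The point holds as an arithmetic contradiction within the Sample size section. At the stated 25% drop-out, 225 per group leaves about 169 evaluable patients, 13 fewer than the stated 182. The target protects 182 only up to about 19% loss.

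The consequence is modest: about 77% power instead of 80% on the calculation that reproduces 182, and 79.9% if no continuity correction is used. The shortfall in numbers rests only on the article's own figures. The 77% also rests on the inference that 182 was continuity-corrected. All the power figures treat patients as independent and so say nothing about the effect of randomising pharmacies.

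**What to change.** Make one of these changes in the Sample size section:

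1. **Keep 450.** State that 25% attrition leaves about 169 per group with about 77% power on the continuity-corrected calculation, or state that 225 per group allows for only about 19% attrition.
2. **Correct the target** to 243 per group, 486 in total.

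In either case, add a sentence saying that the figures correct the drop-out step only and include no allowance for cluster randomisation. Without it, 243 could be read as sufficient for 80% power in this design.

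The first option costs one sentence. The second adds 36 patients to the target, 8.7 per pharmacy instead of 8.0, and needs no change to the recruitment request already made to pharmacists.
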